#### Implementation framework

The study design, and outcome measures are centered in the essential implementation metrics as defined by the RE-AIM framework, which modified to the context of our study (Table 1) [17]. Outcomes will be evaluated through quantitative, qualitative and process measures. This design will allow us to test the following hypotheses:Community-based cervical cancer screening will reach a larger portion of eligible women and be more acceptable to patients and providers than clinic-based testing. (REACH)A community-driven intervention will improve linkage to treatment among women who need treatment after an HPV-positive screening test compared to standard referral. (EFFICACY)We will identify modifiable patient and health system challenges that can be addressed to make health campaign based HPV testing and enhanced linkage to treatment succeed and be sustainable. (ADOPTION & MAINTENANCE)Community-based cervical cancer screening with enhanced linkage to treatment will have a greater population-level health impact as measured in women reached with screening and any necessary treatment, and favorable cost-effectiveness profile compared to clinic-based strategies and standard referral for treatment. (IMPLEMENTATION)

**Table 1 Tab1:** A modified RE-AIM framework to evaluate community health campaign-based cervical cancer screening compared to health-facility based screening

	Dimension Goal	Implementation Question	Hypothesis
Reach	Who is intended to benefit?	How do we reach reproductive-aged women in rural kenya?	A screening strategy offered through community health campaigns in a central location will reach a large proportion of reproductive-aged women.
	How do we reach them?		
Effectiveness	Is the program effective?	Are women getting screened for cervical cancer with HPV?	A community-based strategy allowing for self-testing will be highly acceptable.
	How do we ensure effectiveness?	Are HPV + women successfully linking to treatment?	Innovative, patient and provider-designed strategies will increase the number of women linking to care.
Adoption and Maintenance	How can strategy be maintained after initial implementation and adopted in similar communities?	What are the patient, provider and delivery system processes necessary to ensure consistent service provision?	A screening protocol with a simple, patient-performed test offered as part of a health fair will minimize the costs to the health care system to introduce screening.
	What are the short and long-term health effects in the community?	What is the population-level health impact of screening using HPV self-testing in the CHCs with enhanced linkage to care?	The high number of at -risk women reached through the CHC-base strategy with enhanced linkage to care would produce a greater population-level health impact.
Implementation	What is adherence to the implementation strategy at the delivery level?	Is HPV testing being offered and delivered consistently at the CHC and clinic sites?	Providing testing in a high-volume CHC will reach a large number of women with low staffing and infrastructure needs, and will therefore have a lower cost per woman treated than a standard strategy.
	What are the costs of implementation?	What is the cost per lesion treated?	

#### Participants

Our target population is women living in rural Kenya who are eligible for and would benefit from cervical cancer screening per the Kenya Ministry of Health Guidelines (25–65 years old with an intact uterus and cervix). The study population is women 25–65 years in the twelve communities in the Nyanza Province who access screening during both phases of the trial.

#### Recruitment and consent

Communities participating in the trial provided verbal assent in the planning process with written consent obtained from individuals for screening. Participants were recruited through the community health campaigns and in the clinics. Women within the target age range were invited to attend the cervical cancer educational module. After the health talk, women were asked to provide informed consent by research assistants for a post-module questionnaire and follow-up after screening completion. Women who were not willing to provide informed consent were still able to attend the health talk and have access to the HPV screening strategy assigned to her arm, but were not contacted for the follow-up in-depth interviews or participation in focus group discussions.

#### Primary and secondary endpoints

To determine the **reach** of cervical cancer screening using HPV-testing in community health campaigns compared to clinics, we are using the following metrics: i) the absolute number of women who completed screening in each arm and ii) the proportion of women in each arm who completed screening. The total number of women in each arm is the number of women 25–65 in each community as determined by census data. Secondary outcomes will include iii) the proportion of women who accept screening among women offered at each site and iv) the proportion of women in the clinic-based arm who request clinician-collected specimens.

To determine the **efficacy** of a community-developed strategy to increase treatment access, we will compare the efficacy of the community-based HPV testing with standard versus enhanced linkage to treatment using the following metrics: i) the number of women who receive treatment after screening HPV + in the intervention (Phase 1) compared to the enhanced intervention (Phase 2) and ii) the proportion of HPV-positive women in each arm who complete treatment. Secondary outcomes that address quality of care concerns for the models will include iii) the proportion of women who receive the correct treatment (per Ministry of Health protocol) during a single treatment visit and iv) the average time between HPV testing and access of treatment by arm.

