### Study activities

#### Study preparation

**Community enumeration and randomization:** Prior to the initiation of the cluster randomized trial, we characterized the study communities using a combination of census data, health facility information, mapping and prospective demographic data. We identified communities of approximately 7500 people in three sub-counties of Migori County in western Kenya (population: 350,000, 65 government health facilities). Population estimates were calculated using the 2009 Kenyan census data with population growth estimates for 2015 and 2014, a method that was validated through door-to-door enumeration for a recent large-scale community randomized trial in rural western Kenya [41]. Eligible communities had at least one government health facility with capacity to provide HPV testing, support from community leaders for the community outreach and/or health campaigns, accessibility to health centers via a maintained transportation route and sufficient distance from other potential study sites to limit contamination between arms (buffer zones). As our target group is women in rural communities, we excluded urban settings or communities in which the nearest health center is Migori County Hospital and those that were taking part in a cluster-randomized trial of large-scale community-health campaigns for HIV-testing [41]. We conducted unmatched randomization using a random number generator on Stata 10. The unmatched design will allow us to consider the relationship between community-level factors and our outcomes of interest. After communities were chosen, population estimates were refined through household enumeration done by community health workers assigned to villages and sub-locations within the communities.

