#### Statistical analysis

*Preliminary Analysis:* For each outcome, we will produce descriptive statistics (frequencies, proportions, etc.) overall, across clusters of interest (community, clinic, provider, etc.), and over time. We will also graph these data to identify visual trends.
*Primary and Secondary Analysis:* Although this is a community-level intervention, the main outcomes will be analyzed at the individual level. We will compare the number and proportion of women who screen for HPV (reach) and who get treated for a positive HPV test (efficacy) in communities assigned to community vs. clinic-based testing using generalized estimating equations to account for the correlation among observations within communities. Efficacy: We will employ a log link and Poisson distribution with an offset term to represent the size of each community.
*Power calculations:* We anticipate being able to observe a 30% difference in overall screening uptake between the control and intervention arms, a conservative estimate relative to previous cluster randomized trials. The power calculations assume an alpha of 0.05, a beta of 0.20, and an intracluster correlation coefficient of 0.072 for screening and 0.11 for treatment, based on calculations from a cluster-randomized trial of HPV efficacy [5].

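### The efficacy model divides women treated by community size, so it mixes reach with linkage; the proportion of HPV-positive women treated should be the single primary efficacy metric.

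*Protocol article*

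**What the plan says.** Under Primary and secondary endpoints, the efficacy aim has two lead metrics. The first is "the number of women who receive treatment after screening HPV + in the intervention (Phase 1) compared to the enhanced intervention (Phase 2"). The second is "the proportion of HPV-positive women in each arm who complete treatment". Only items iii and iv are called secondary, so the count and the proportion are both primary by position and neither comes first. The reach aim has the same layout: "the absolute number of women who completed screening in each arm" beside "the proportion of women in each arm who completed screening". There the denominator is defined: "The total number of women in each arm is the number of women 25–65 in each community as determined by census data".

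The Statistical analysis section says that both number and proportion will be compared, for screening and for treatment, between communities assigned to campaign and clinic testing, using generalized estimating equations. It then states one model: "Efficacy: We will employ a log link and Poisson distribution with an offset term to represent the size of each community". The article gives no other offset.

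The Study design section says that HPV-positive women in all Phase 1 communities received the same standard referral. The second hypothesis, under Implementation framework, concerns linkage among women who need treatment after a positive test.

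**The concern.** The efficacy aim asks whether HPV-positive women get to treatment. Its natural denominator is HPV-positive women. An offset for community size puts all resident women in the denominator, so the model estimates treated women per resident woman. That quantity rises when more women are screened, even if the chance of treatment after a positive test is unchanged. It can also stay flat while linkage improves, if fewer women are screened.

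At stake is what the trial may conclude about the enhanced linkage strategy. A result labelled efficacy could be produced entirely by the screening strategy, or a real linkage gain could be cancelled by lower turnout. Because the count and the proportion are unranked, the article does not say which would stand if they disagreed.

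**Working it through.** **Inputs from the protocol (Sample size).** About 1000 women per community; six communities per arm; 510 women screened per campaign community and 210 per clinic community.

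**Assumed inputs (not in the document).** HPV prevalence, linkage rates and Phase 2 reach.

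**1. The plan's own figures.** 6 × 510 = 3060 and 6 × 210 = 1260, as stated. Planned reach is 510/1000 = 51% and 210/1000 = 21%.

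**2. What the offset model estimates.**
- Women treated = residents × reach × prevalence × linkage.
- With community size as offset, the modelled rate is treated/residents = reach × prevalence × linkage.
- The rate ratio between two groups is (reach ratio) × (prevalence ratio) × (linkage ratio). Only the last term is the efficacy question.

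**3. Phase 1, campaign against clinic.** Take equal prevalence and identical linkage. The rate ratio is 0.51/0.21 = 3060/1260 = 2.43, whatever the common prevalence and linkage. As an illustration, assume prevalence 20% and linkage 40%:
- Campaign: 3060 × 0.20 = 612 positive; 612 × 0.40 = 244.8 treated.
- Clinic: 1260 × 0.20 = 252 positive; 252 × 0.40 = 100.8 treated.
- Offset by 6000 residents per arm: 244.8/100.8 = 2.43.
- Offset by HPV-positive women: 0.40/0.40 = 1.00.

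**4. Phase 1 intervention against Phase 2 enhanced intervention.**
- If Phase 2 reach is 40% (assumed) instead of 51%, equal counts require a linkage ratio of 0.51/0.40 = 1.275, or 27.5% higher.
- A hidden gain: let linkage rise from 40% to 60% while the number screened falls from 3060 to 2040, at 20% prevalence (all assumed except 3060). Phase 1 treats 3060 × 0.20 × 0.40 = 244.8; Phase 2 treats 2040 × 0.20 × 0.60 = 244.8. The count ratio is 1.00 although the linkage ratio is 1.5.
- A spurious change: hold linkage and prevalence equal and let the Phase 2 number screened be 2000 or 4500. These are the two resource ceilings in the Sample size section, borrowed here only as a range. The treated ratio is 2000/3060 = 0.65 or 4500/3060 = 1.47.

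A community-size offset removes none of this, since the number screened is not community size.

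**5. Reach, for the clarification only.** The power statement concerns screening uptake, a proportion. I read the 30% difference as 51% against 21%. With 1000 women per community and ICC 0.072, the design effect is 1 + 999 × 0.072 = 72.9 and the effective size is 6000/72.9 = 82.3 per arm. The standard error is √[(0.51 × 0.49 + 0.21 × 0.79)/82.3] = 0.071, so the difference is 0.30/0.071 = 4.2 standard errors. Power is about 97% (noncentral t, 10 df, two-sided alpha 0.05, sidedness assumed). Making the reach proportion primary costs no power.

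**The case against.** The strongest reply is that the right metric is already listed: the proportion of HPV-positive women treated appears in the endpoints. The counts also have a purpose, since the fourth hypothesis measures population impact in women reached with screening and treatment. Both points stand. They argue for keeping the count as an impact measure, but they do not make it a measure of linkage or rank the two metrics.

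One could add that individual-level estimating equations on treated yes/no among HPV-positive women would give the proportion, or that the efficacy label on the Poisson sentence is misplaced. Either may be the intention, but the text attaches the community-size offset to efficacy and needs correcting in each case.

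A reader might infer that the reach result is equally compromised: no offset is stated for the reach count, and "We conducted unmatched randomization using a random number generator on Stata 10" means that arm populations are not balanced by design. The document does not support that. The reach proportion and its census denominator are listed, the first hypothesis and the power basis are on the proportion scale, and a missing offset for reach is detail that a condensed article may omit. Size imbalance is also too small to matter at the planned effect. With an assumed coefficient of variation of community size of 0.15–0.25, simulated six-against-six allocations put arm populations more than 10% apart in 27–51% of cases, with a 95th percentile of 1.18–1.33, against a planned ratio of 2.43.

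Nor does the difference between communities of about 7500 people (Study preparation) and 5000 (Sample size) show variation between communities; it is a conflict between two planning statements. A reader might also infer two chances of success per aim, but the article states no rule that either metric suffices.

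**Conclusion.** The point holds for the efficacy aim. As written, the model estimates reach × prevalence × linkage. In the campaign against clinic comparison, identical linkage would appear as a ratio of about 2.43; this follows from the plan's own screening figures and assumes only equal HPV prevalence. In the between-phase comparison, the direction and size of the distortion depend on Phase 2 turnout, which the document does not give; the 27.5% figure rests on an assumed reach of 40%.

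The article is also inconsistent about which communities serve in Phase 2. The Abstract speaks of 18 communities and a further six, whereas Study design reuses the six Phase 1 controls and Participants counts twelve. If the controls are reused, they have already been offered screening once, which makes a different number screened more likely. The dependence on the number screened exists either way.

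For reach, only a minor clarification is warranted.

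**What to change.** - **Efficacy:** name the proportion of HPV-positive women who complete treatment as the single primary metric. Model it with HPV-positive women as the denominator: binomial, or Poisson with log(number HPV-positive) as offset, keeping the estimating equations for clustering. Replace the community-size offset in the efficacy sentence.
- **Number treated:** report it, or treated per resident woman, as population impact under the fourth hypothesis.
- **Reach:** state that the proportion of women aged 25–65 screened is primary, and that any count model uses log(women aged 25–65) as offset and estimates the same quantity.
- **Phase 2 communities:** reconcile the Abstract with Study design and Participants.
- **Timing:** date and justify the change. Trial status says that Phase 1 enrolment ended in September 2016 and that results were being shared.

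The cost is a few sentences in the endpoint and analysis sections and the loss of one nominal primary result. The proportion also describes only women who came for screening, so the impact measure should be reported beside it.

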#### Data collection

We collected data on both screening and linkage to treatment from both control and intervention communities in Phase 1. Data was collected by members of the research team and entered into pre-programmed tablet computers using OpenDataKit software (ODK™),(https://opendatakit.org) which had been used by this research team for the past several years. Programming included checks for range, structure, and internal consistency. During the community-health campaigns, data was collected directly from providers and participants into the tablets and was transferred daily via a secure electronic transfer to our data center facility in Kisumu, Kenya and stored on a secure server. To capture visits and outcomes from clinic-based screening and facility treatment, a member of the research team visited each clinical facility on a weekly basis to enter data from Ministry of Health registers and study-specific forms into the tablets. Data transfer from clinical-sites took place weekly. The same data collection procedures will be applied in Phase 2.

#### Implementation consistency

All four basic components of the intervention (outreach/education, HPV-testing, notification of results and linkage to treatment) were monitored throughout Phase I of the trial to ensure maintained fidelity to the protocol and quality of service and message delivery. Quantitative outcome measures, as well as the process measures listed below assessed continued fidelity of the intervention as offered. Qualitative data from in-depth interviews, focus-group discussions and process measures will provide a more complete picture about subtle but important factors that may influence the actual service delivery and uptake.

#### Sample size

Using estimates from the 2009 Kenya census [45] with projected population growth for 2015 and results from recent community-wide census enumeration carried out by a cluster randomized trial in an adjacent district [46], we have estimated the total available population of women to be approximately 1000 per community of 5000. The estimates for attendance at community health campaigns (60% or 600 women) and clinics (30% or 300 women) and screening uptake were based on our formative work, community health campaign attendance in adjacent districts, and prior studies of self-collected HPV testing [27, 28, 47]. Our assumptions were that (1) attendance would be higher at community health campaigns and (2) screening uptake would be higher among women attending community health campaigns because most women attend based on outreach messaging around cervical cancer. These assumptions suggested a study population of 510 women per community accessing testing through community health campaigns and 210 accessing screening through clinics. For Phase 1, the total number of women accessing screening in the six communities randomized to community health campaigns would be 3060 and 1260 in communities randomized to clinic-based testing. We used these conservative estimates for sample size calculations (see below), but allocated resources for up to 4500 women in the community-testing arm and 2000 women in the clinic-based screening arm to ensure continuity of study activities. We also enrolled all providers and targeted key ministry of health stakeholders for quantitative and qualitative assessments of barriers and facilitators to care. A representative subset of this group were invited to participate in meetings to develop the enhanced linkage intervention.

#### Statistical analysis

*Preliminary Analysis:* For each outcome, we will produce descriptive statistics (frequencies, proportions, etc.) overall, across clusters of interest (community, clinic, provider, etc.), and over time. We will also graph these data to identify visual trends.
*Primary and Secondary Analysis:* Although this is a community-level intervention, the main outcomes will be analyzed at the individual level. We will compare the number and proportion of women who screen for HPV (reach) and who get treated for a positive HPV test (efficacy) in communities assigned to community vs. clinic-based testing using generalized estimating equations to account for the correlation among observations within communities. Efficacy: We will employ a log link and Poisson distribution with an offset term to represent the size of each community.
*Power calculations:* We anticipate being able to observe a 30% difference in overall screening uptake between the control and intervention arms, a conservative estimate relative to previous cluster randomized trials. The power calculations assume an alpha of 0.05, a beta of 0.20, and an intracluster correlation coefficient of 0.072 for screening and 0.11 for treatment, based on calculations from a cluster-randomized trial of HPV efficacy [5].

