In Phase 1 of this study, we compared two implementation strategies that incorporated these four evidence-based elements of screening. Based on our preliminary data, we found that reaching and attending a health facility for preventive care was a significant barrier to screening for many women. Therefore, the main objective was to compare a model offering screening in brief, high throughput community health campaigns to that of a standard of care in which screening was offered in local health facilities using the metrics defined in the modified RE-AIM framework.

In Fig. 1, we present an overall schema of the cluster-randomized trial. In Phase 1, six communities were randomized to the intervention: HPV screening carried out in **community health campaigns**. The remaining six were comparison communities: HPV testing offered in **government health facilities**. HPV-test positive women in all communities were referred to the County hospital for immediate treatment, which is considered standard linkage to treatment.

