**Fig. 1 Fig1:**
[figure not shown]
Two-phase cluster-randomized trial design

Development of an enhanced strategy for linkage to treatment: After Phase 1, we have an “inter-phase intervention development” period in which we are evaluating the results from the trial. The outcomes from the qualitative and quantitative measures will be used to refine the screening intervention using context-specific details and develop an enhanced strategy for linkage to treatment. Although we have identified factors that enable and inhibit women’s access to treatment, we chose to wait until after Phase 1 for the development of the enhanced strategy for linkage to treatment in order to truly work in partnership with the community. The delayed development of the linkage to treatment strategy has allowed us obtain a baseline measure of the efficacy of standard referrals and identify factors that would influence women’s access to care in this setting.

After developing the strategy for enhanced linkage, we will pilot and then test the linkage to treatment strategy as part of an “enhanced intervention” in the six communities that served as controls in Phase 1. Using these communities for the enhanced intervention increases the efficiency of the study in two ways: i. we will have done community enumeration and engagement, and ii. we will compare linkage to treatment outcomes from these “enhanced intervention” communities to the intervention communities from Phase 1.

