**HPV testing:** While HPV test results are not the primary outcome for this study, the accuracy and reproducibility of measurements are essential for outcomes in both arms and for modeling the impact of the implementation strategies in larger populations. We tested the DNA for 14 HPV types (16, 18, 32, 33, 35, 39, 45, 51, 52, 56, 58, 59 and 68) using CareHPV™ testing system. Collected specimens were transported daily from the CHCs and weekly from the health facilities to the study lab at Migori County Hospital. Tests were run in batches of 90, with a turnover time of approximately 1–2 weeks for results.
**Notification of HPV results:** HPV test results were preferentially sent to women via text message with instructions about appropriate follow-up as recommended by the Kenya Ministry of Health guidelines. Messages were developed by key stakeholders and women from the target population during the focus group discussions. Women who did not have access to a phone, or did not wish to receive their results by SMS could opt for a return visit to the clinic, or a home visit.
**Standard referral for treatment (both arms, Phase 1):** Women who were HPV-positive were referred to Migori County Hospital for a visual exam with acetic acid and treatment with cryotherapy per the WHO guidelines [44].
**In-depth participant interviews and focus groups:** We conducted semi-structured interviews with randomly selected participants in both arms at three key points in the cervical cancer prevention cascade: screening delivery (*n* = 30), notification of results (n = 30) and treatment access (all). Participants were contacted either in person or by phone, and interviews conducted in person by experienced qualitative interviewers in the local language using interview guides developed by the research team. Topics explored in these interviews will elucidate ways to make cervical cancer screening more acceptable and accessible to women. Interviews captured quantitative data about women’s participation in various aspects of the prevention cascade. Interviewers then explored women’s perspectives of their experience with the intervention and explanatory factors related to the decisions to access screening and treatment through open-ended questions. Among women who did not access treatment, we probed for factors or strategies that would allow them to link to care in the future.

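### The efficacy analysis as written compares testing venues that shared one standard referral, with a community-size offset, so it does not test enhanced linkage and mainly reflects screening reach

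*Protocol article*

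**What the plan says.** Three places in the Protocol article define the efficacy question in the same way.

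- Implementation framework, the hypothesis labelled efficacy: "A community-driven intervention will improve linkage to treatment among women who need treatment after an HPV-positive screening test compared to standard referral".
- Primary and secondary endpoints: "we will compare the efficacy of the community-based HPV testing with standard versus enhanced linkage to treatment". The groups for the count of treated women are given as "in the intervention (Phase 1) compared to the enhanced intervention (Phase 2"), and the second metric is "the proportion of HPV-positive women in each arm who complete treatment".
- Study design and setting: the enhanced intervention is to be tested "in the six communities that served as controls in Phase 1", and its linkage outcomes are to be compared with those of the Phase 1 intervention communities.

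The Statistical analysis section, under Primary and Secondary Analysis, says something different. It compares women "who get treated for a positive HPV test (efficacy) in communities assigned to community vs. clinic-based testing" by generalized estimating equations. For efficacy it specifies a log link, a Poisson distribution and an offset for community size. It mentions neither Phase 2 nor the enhanced intervention.

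On the referral given in Phase 1 the article is explicit. Study design and setting states: "HPV-test positive women in all communities were referred to the County hospital for immediate treatment, which is considered standard linkage to treatment". The Phase 1 activities carry the heading "Standard referral for treatment (both arms, Phase 1").

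**The concern.** There are two linked faults.

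1. **The contrast.** Under the endpoint section, both efficacy groups use community-based testing and differ in linkage strategy. Under the analysis section, the groups differ in testing venue, and in Phase 1 both had the same linkage strategy. The analysis as written cannot estimate what the efficacy hypothesis asks.
2. **The offset.** Dividing by community size gives treated women per head of population. The hypothesis, and the second efficacy metric, concern women who have tested positive. A population offset lets the number screened drive the result.

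At stake is one of the trial's two main outcomes. Run as written, the result carrying the efficacy label would be expected to favour community testing even if linkage were identical in the two arms. The finding on reach would then be reported a second time under another name.

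**Working it through.** **Step 1. The two contrasts side by side.**

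| | Primary and secondary endpoints | Statistical analysis |
|---|---|---|
| Group A | Phase 2: community testing, enhanced linkage | Communities assigned to community testing |
| Group B | Phase 1: community testing, standard linkage | Communities assigned to clinic testing |
| What differs | Linkage strategy (and calendar period) | Testing venue |
| Denominator | HPV-positive women (second metric) | Community size, through the offset |

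In Phase 1 the linkage strategy is the same in both groups of the right-hand column.

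**Step 2. Inputs and the plan's own figures.** The Sample size section gives about 1000 women per community, 510 screened per community through campaigns and 210 through clinics, with six communities per arm.

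- 6 × 510 = 3060, as stated.
- 6 × 210 = 1260, as stated.

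The article gives no HPV prevalence, no treatment proportion under standard referral and no target effect on linkage. These are assumptions below: prevalence h from 10% to 40%, equal in all groups; standard linkage s of 30% or 40%; enhanced linkage e of 60% or 70%.

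**Step 3. What the written model targets.** With n women screened in a community of N women, the expected treated rate is n × h × s / N. The ratio of community to clinic testing is

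(510 × h × s / 1000) / (210 × h × s / 1000) = 510/210 = 2.43.

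Both h and s cancel. Treated women per 1000, with s = 30%:

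| h | Community testing | Clinic testing | Ratio |
|---|---|---|---|
| 10% | 15.3 | 6.3 | 2.43 |
| 20% | 30.6 | 12.6 | 2.43 |
| 30% | 45.9 | 18.9 | 2.43 |
| 40% | 61.2 | 25.2 | 2.43 |

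The quantity e does not appear. At equal prevalence, linkage in the community arm would have to fall to 210/510 = 0.41 of that in the clinic arm before the ratio came down to 1.

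**Step 4. The same groups, with HPV-positive women as denominator.** Under equal linkage the ratio is s/s = 1.0. This removes reach, but e is still absent.

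**Step 5. The contrast in the endpoint section.** At equal reach and prevalence, the ratio is (510 × h × e) / (510 × h × s) = e/s:

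- s = 30%, e = 60%: 2.0
- s = 40%, e = 70%: 1.75

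This contrast does carry the enhanced-linkage effect. If the community-size offset were kept and reach differed between phases, the ratio would become (reach in Phase 2 / reach in Phase 1) × e/s. Changing the groups alone is therefore not enough; the offset must change too.

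**The case against.** The strongest reply is that the intended contrast is already fixed in the endpoint section, the design section and the hypothesis. On that view, one compressed sentence in a journal article fails to repeat it, and the Phase 2 model may stand in the full protocol or in an analysis plan not shown here. The first part stands: the intended comparison can be recovered from the article. The second does not. An omitted model could be left to another document, but here the article states a contrast, calls it efficacy, and contradicts its own definition.

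A second reply is that the clinic-assigned communities are the ones that later receive the enhanced intervention, and that the analysis sentence is not expressly limited to Phase 1. But the sentence groups communities by testing mode. Both efficacy groups in the endpoint section use community testing, so a community-versus-clinic label cannot describe them.

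A third reply is that treatment by testing venue is worth knowing. It is: linkage data were collected in both Phase 1 arms, and the fourth hypothesis concerns women reached with screening and any necessary treatment. A count per population also fits the first efficacy metric, the number treated. This supports keeping the comparison under another name, but not using it as the efficacy test.

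Three stronger readings are tempting, and the documents do not support them.

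- A reader might infer that the trial has no valid efficacy comparison at all. The endpoint and design sections give one.
- A reader might infer that a null Phase 1 result would be taken as failure of enhanced linkage. The article says that this strategy is developed only after Phase 1, which makes the misreading unlikely.
- A reader might infer that the written test at least isolates the effect of venue on linkage. With the community-size offset it does not, because reach enters the estimate.

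**Conclusion.** The point holds as a contradiction within the Protocol article. The Statistical analysis section gives the efficacy label to a contrast that cannot test the efficacy hypothesis, and the stated offset makes that contrast mainly a measure of screening reach. The expected ratio is 2.43 with no linkage difference. That figure rests on the planned 510 and 210 screened per community, equal community size, and equal HPV prevalence and linkage in both arms. It does not depend on the level of prevalence or of linkage. Unequal prevalence or linkage would multiply 2.43 by the corresponding ratio.

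The contradiction itself needs no figure. No corrected sample size or power for linkage can be derived, because prevalence, baseline treatment and the target effect are not given. The defect lies in the analysis wording and its denominator. It does not extend to the choice of endpoint or to the data collected.

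**What to change.** Bring the Statistical analysis section into line with the endpoint section.

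- **Efficacy analysis:** the proportion of HPV-positive women who complete treatment, Phase 2 enhanced-intervention communities versus Phase 1 intervention communities, with community as the cluster.
- **Denominator:** HPV-positive women. If the Poisson model is kept, the offset should be the number of HPV-positive women and not community size.
- **Limitation to state:** the two groups come from different calendar periods, so a change over time cannot be separated from the effect of enhanced linkage by this comparison alone.
- **Secondary analysis:** keep treatment by community versus clinic testing in Phase 1 under its own label, and say whether it is per HPV-positive woman or per population.

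The cost is wording only. The Data collection section says that linkage data were collected in both Phase 1 arms and that the same procedures will apply in Phase 2. According to the Trial status section, Phase 1 screening is finished and the enhanced strategy is still being designed. The change can therefore be made before any Phase 2 outcome exists.
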